**Methods:**

Twenty volunteers between the age of 40-59 years old, diagnosed, and confirmed to be suffering from vestibular neuritis and vertigo will be used in this study. Gaze stability exercises will be performed while patients are in a seated position. Each exercise will last for 30 seconds and be done in phases that included; eyeball movement, saccadic eye movement, pursuit eye movement, vergence eye movement, and vestibular-ocular reflex exercise. Balance exercises will be performed in a standing position including both static and dynamic training with or without closing eyes. The following outcome measures for each participant will be assessed pre-and post-treatment after completing four weeks of intervention. They include; Arabic version of Activities-Specific Balance Confidence Scale (A-ABC scale), Berg Balance Scale (BBS), and Katz Index of Independence in Activities of Daily Living (Katz ADL). The findings will then be subjected to statistical methods and data analysis using the SPSS toolkit.

**Key words:** vestibular neuritis, gaze stability, balance exercise

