# **1 Background Information**

Balance and stability are important components for daily activities. Individuals need appropriate posture and coordination of various body parts for them to perform basic movements needed when doing various activities. The body requires a strong balance to perform day-to-day activities such as walking up and downstairs, bending, as well as lifting things from the ground. Lack of this balance, which can occur because of ear infections, accidents, and aging, generally can result in decreased quality of life. Nichols-Larsen et al., (2016) mentioned that vestibular neuritis is the second most common cause of vertigo and patients are complained of balance disturbance after head movements. Most healthcare facilities as well as health fitness centers use exercises to improve balance and stability in patients with balance problems. Examples of such balance exercises include gaze stability exercises. This literature reviews the effectiveness of gaze stability with balance exercises in enhancing balance, activities of daily living and reducing the risk of falling among patients suffering from vertigo due to vestibular neuritis in Riyadh.

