## **1.4 Objectives**

This literature aims to assess whether conducting gaze stability with balance exercises has an improvement influence on balance and reducing falling incidence. Moreover, to study the impact of applying combination of gaze stability and balance exercises to improve activities of daily living in patients suffering from vertigo with vestibular neuritis in Saudi Arabia.

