# **2 METHODOLOGY**

## **2.1 Study design**

This research is experimental with Pre-post cohort design, Pilot clinical trial, by using telerehabilitation.

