### **2.2.1 Inclusion/exclusion criteria**

A convenience volunteers of middle-aged adults of 40-59 years old are diagnosed with vestibular neuritis and vertigo. Participants should not be either with a previous history of neurological diseases or brain surgery affecting equilibrium. Both male and female are cognitively intact. Subjects with medical issues, e.g., hypertension and diabetes, are undertaking medication regularly. Independent participants or those requiring reasonable assistance, but with balance disturbance in daily living activities and transferring, having Berg Balance Scale between 21-56 are included in the study.

However, subjects with the inability to follow instructions or completely dependent on the assistive device during mobility have been eliminated from the study. Participants with chronic dizziness diagnosed specifically with benign paroxysmal positional vertigo (BPPV), migraine-associated vertigo, or Meniere's disease are excluded. The research will be applied locally in Saudi Arabia, and all participants will sign a consent form approved by the Ethics Committee of King Saud University.

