## **2.5 Outcome measures**

The following outcome measures for each participant will be evaluated before the commencement of treatment and at the end of four weeks of training. They include; Arabic version of Activities-Specific Balance Confidence Scale (A-ABC scale) to measure patient self-confidence for performing activities of daily living without losing balance. Permission has been granted from original author [name] by email to use the Arabic version of the ABC scale. It has proved its good reliability and validity and can be used with the Arab population's vestibular disorders (Alghwiri AA, Alghadir AH, Al-Momani MO and Whitney SL, 2015) (figure 2) (Appendix 3).

In addition, Berg Balance Scale (BBS) to evaluate static balance and fall risk in adult. It has shown good reliability and validity with vestibular patients too (Alghwiri AA, Alghadir AH, Al-Momani MO and Whitney SL, 2015) (figure 3) (Appendix 3).

Moreover, Katz Index of Independence in Activities of Daily Living (Katz ADL) to define problems in performing ADLs. It has demonstrated excellent validity and reliability to assess the ability to perform daily living activities independently in adult and older community-dwelling populations (Hopman-Rock M, van Hirtum, H, de Vreede P and Freiberger E, 2019) (figure 4) (Appendix 3).

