## **2.6 Data analysis**

Data will be collected, tabulated, and analyzed using SPSS version 25. The descriptive data will be represented as mean (*M*) and standard deviation (*SD*). Paired *t*-test will be run to compare pre-intervention and post-intervention scores of A-ABC, BBS& Katz-ADL for each participant. Pearson’s r regression will be used to detect the linear association between variables. Results will be statistically significant at p <0.05.

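### Section 1.4 aims at a lower incidence of falls, but none of the three outcomes counts falls, so that aim cannot be answered

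*Protocol*

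**What the plan says.** Protocol section 1.4 asks whether the combined exercises have an effect that "has an improvement influence on balance and reducing falling incidence". Section 1 puts the fall-related goal differently, as "reducing the risk of falling among patients suffering from vertigo due to vestibular neuritis". The study aim in the abstract does not mention falls.

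Section 2.5 names three instruments: the Arabic A-ABC, the BBS and the Katz ADL. The abstract names the same three. They "will be evaluated before the commencement of treatment and at the end of four weeks of training". Only one is tied to falls: "Berg Balance Scale (BBS) to evaluate static balance and fall risk in adult". Section 2.6 plans a paired t-test to "compare pre-intervention and post-intervention scores of A-ABC, BBS& Katz-ADL for each participant", and a correlation analysis whose variables it does not name.

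On design, section 2.1 states: "This research is experimental with Pre-post cohort design, Pilot clinical trial, by using telerehabilitation". The sample is 20 people in one group. On eligibility, section 2.2.1 admits those with balance disturbance "having Berg Balance Scale between 21-56 are included in the study". Section 2.4 and Table 1 of the appendix have participants do the standing and walking exercises with eyes open in weeks 1 and 2, and with eyes closed in weeks 3 and 4. Section 2.4 also provides weekly remote follow-up supervised by the researcher, without saying what that follow-up covers.

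**The concern.** Fall incidence and fall risk on a scale are different quantities. The first needs falls to be counted over a defined period; the second is a score at a point in time. Section 1.4 names the first, while the outcome and analysis sections deliver only the second. A later analysis plan cannot repair this, because it can only analyse what the protocol collects.

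At stake is what the trial may conclude. If section 1.4 stands, the report must either leave a stated aim unanswered or answer it with a change in BBS, from a single group without a control, presented as if it were a change in falls.

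A smaller, separate matter is harm. The sections on intervention, outcomes and analysis do not say that falls or other adverse events are recorded, although the eyes-closed phase is done remotely by people chosen for having balance problems.

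**Working it through.** The main check is to follow the fall aim through the protocol.

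1. **Aim (1.4):** incidence of falls. This needs a count of falls and a period of observation, and a comparison period if a reduction is to be claimed.
2. **Outcomes (abstract; 2.5):** A-ABC is a confidence score, BBS a balance and fall-risk score, and Katz ADL an independence score. Outcomes that count falls: 0 of 3.
3. **Timing (2.5):** two assessments, at baseline and at the end of week 4. No fall history before treatment and no fall diary during it is specified.
4. **Analysis (2.6):** the pre-post comparison is of the three scores. The correlation analysis cannot include falls, because no fall variable is collected.
5. **Other wording (1; 2.5):** both speak of risk. Section 1.4 is alone in naming incidence.

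So the chain breaks between steps 1 and 2, and section 1.4 is the part out of line.

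**Would adding a fall count rescue the aim?** The protocol gives no fall rate, so the values here are assumptions. Suppose each participant's chance of any fall in the 4 weeks before treatment is p1, this halves to p2 = p1/2 during the 4 treatment weeks, and the two periods are independent within a person. Take n = 20, two-sided alpha 0.05 and an exact McNemar test. The chance of a discordant pair is p1(1 − p2) + p2(1 − p1). At least 6 discordant pairs, all in one direction, are needed for significance: 2 × 0.5^6 = 0.031, whereas 2 × 0.5^5 = 0.0625.

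| p1 → p2 | Chance of discordant pair | Expected discordant pairs (× 20) | Power |
| --- | --- | --- | --- |
| 10% → 5% | 0.095 + 0.045 = 0.14 | 2.8 | 0.5% |
| 20% → 10% | 0.18 + 0.08 = 0.26 | 5.2 | 4.1% |
| 30% → 15% | 0.255 + 0.105 = 0.36 | 7.2 | 9.8% |
| 40% → 20% | 0.32 + 0.12 = 0.44 | 8.8 | 16.4% |
| 50% → 25% | 0.375 + 0.125 = 0.50 | 10.0 | 24.3% |

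Even if half the participants fell in the month before treatment, a test of a halving would succeed about one time in four. Without a control group, a fall in the rate could not be credited to the exercises in any case. The aim should therefore be brought to the outcome, and not the reverse.

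**Cost of asking about falls at existing contacts:** 20 participants × 4 weeks = 80 contacts. At an assumed 2 to 3 minutes each, this is 80 × 2 = 160 minutes (2.7 hours) to 80 × 3 = 240 minutes (4 hours).

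**The case against.** The strongest reply is that the contradiction is one loose word. The abstract's study aim does not mention falls, section 1 speaks of risk, section 2.5 assigns the BBS to fall risk, and section 2.6 plans no analysis of incidence. This is probably how the word arose. It limits the seriousness of the point but does not remove it: the objectives section defines what the trial claims to answer, and as written it names something the trial cannot answer. A reader might go further and infer that the sponsor plans to report a BBS change as fewer falls. The protocol does not say so; the risk is only that the present wording leaves room for it.

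On recording, the reply is that silence is an omission and not an error, and that the weekly supervised contact may well bring events to light. That largely stands. Title and consent pages are not available for review and could hold a safety statement, and section 2.7 sends the proposal to ethics review before the start. Several features also lower the risk: the firm surface, two eyes-open weeks first, and the exclusion of people who depend completely on an assistive device, cannot follow instructions, or have earlier neurological disease or brain surgery affecting equilibrium. Participants must be cognitively intact. A BBS of 21 is only the lower end of the admitted range, and nothing shows how many would be near it. A reader might infer that falls will go unasked or that safety is unmonitored; the documents do not support that. They support only that sections 2.4 to 2.6, as shown, give such events no stated place in the data.

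**Conclusion.** The point holds for the aim. The incidence of falls named in section 1.4 cannot be answered from what the protocol collects and analyses: 0 of 3 outcomes counts falls. This rests on the text alone and needs no assumed figure; confidence is high. It should be corrected before the trial reports, but it is not fatal. It does not mean that the trial measures nothing but fall risk, since A-ABC and Katz ADL address balance confidence and daily activities, and the three pre-post score comparisons are untouched.

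The absence of stated fall and adverse-event recording is a secondary point, held with moderate confidence, because the content of the weekly contact is not described and some pages are not available.

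The power figures of 0.5% to 24.3% depend on assumed fall probabilities, a halving, and independence within a person. They serve only to show why the remedy is a change of wording and not a new tested endpoint.

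**What to change.** **Main change.** In section 1.4, replace the incidence phrase with *fall risk as measured by the BBS*. This agrees with sections 1 and 2.5 and changes no visit, measurement or test. Its cost is a more modest objective.

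**Secondary addition.** In sections 2.4 and 2.5, state that falls and adverse events are asked about and recorded at each weekly remote contact already planned. In section 2.6, report the number of events and the number of participants affected, descriptively, with no test and no claim of reduced incidence. There are no new visits. The cost is about 2.7 to 4 hours of contact time in total under the assumed 2 to 3 minutes per contact, one extra table, a short definition of what counts as an event, and any follow-up that a reported event calls for. The data would rest on self-report, which should be stated with the results.

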# **2 METHODOLOGY**

## **2.1 Study design**

This research is experimental with Pre-post cohort design, Pilot clinical trial, by using telerehabilitation.

## **2.2 Participants**

Middle-aged adults of 40-59 years old suffering vertigo due to vestibular neuritis. Through the following criteria, all participants will be eligible to attend the study.

### **2.2.1 Inclusion/exclusion criteria**

A convenience volunteers of middle-aged adults of 40-59 years old are diagnosed with vestibular neuritis and vertigo. Participants should not be either with a previous history of neurological diseases or brain surgery affecting equilibrium. Both male and female are cognitively intact. Subjects with medical issues, e.g., hypertension and diabetes, are undertaking medication regularly. Independent participants or those requiring reasonable assistance, but with balance disturbance in daily living activities and transferring, having Berg Balance Scale between 21-56 are included in the study.

However, subjects with the inability to follow instructions or completely dependent on the assistive device during mobility have been eliminated from the study. Participants with chronic dizziness diagnosed specifically with benign paroxysmal positional vertigo (BPPV), migraine-associated vertigo, or Meniere's disease are excluded. The research will be applied locally in Saudi Arabia, and all participants will sign a consent form approved by the Ethics Committee of King Saud University.

## **2.3 Sample size**

Twenty convenient volunteers of middle-aged adults of 40-59 years old (n=20) are diagnose with vestibular neuritis and vertigo. The sample size is the same as previous studies (Roh and Lee, 2019).

## **2.4 Intervention**

The gaze stability exercises (GSEs) and balance exercises (BE) are described by Roh& Lee (2019) and Khanna& Singh (2014), respectively. This research is reconstructed by combining two forms of exercises (GSEs)& (BE). Participants with vestibular neuritis and vertigo will be practicing a combination of gaze stability exercise (GSEs) and balance exercises (BE).

Gaze stability exercises are included in five phases: eyeball movement, saccadic eye movement, pursuit eye movement, vengeance eye movement, and vestibular-ocular reflex exercise (figure 1) (Appendix 2) (Roh and Lee, 2019). The eyeball exercise moves the eyes to a different direction slowly while they are closed to the left and right, up and down, rotation movements (Roh and Lee, 2019). The saccadic eye movement exercise moves the eyes as quickly as possible between the stationary points with a fixed head (Roh and Lee, 2019). The pursuit eye movement exercise by tracking slowly moving target with the eyes without moving head (Roh and Lee, 2019). The vergence eye movement exercise includes tracking the moving target from 5 cm close to eye level to as far as possible, both backward and forward (Roh and Lee, 2019). The vestibular-ocular reflex exercise keeps the eyes on the fixed point while moving the head from left to right (Roh and Lee, 2019). Gaze stability exercises will be performed while patients are seated, and each exercise lasts for 30 seconds.

Balance exercises, both static and dynamic with or without closing eyes, are recommended to improve postural stability (Khanna and Singh, 2014). In the first two weeks, patients will perform balance exercises with opening eyes, and then in the next couple of weeks, participants will do the same exercises with closing eyes (table 1) (Appendix 1). It involves standing on a firm surface with feet apart, heel stand, toe stand, marching on a firm surface, semi tandem stand, walking forward and backward with a normal support base (Khanna and Singh, 2014).

This intervention of gaze stability with balance exercises will be given as scheduled in the treatment plan (table 1) (Appendix 1) (Roh and Lee, 2019). It will be applied twice each alternative day with ten repetitions for a total treatment period of four weeks. Each session will last for 45-60 minutes. Rest interval is between two groups of exercises for five minutes. Warm-up and cool down for five minutes is applicable before and after completing the treatment session. The patients will be followed up weekly through tele rehabilitation under the supervision of the researcher.

## **2.5 Outcome measures**

The following outcome measures for each participant will be evaluated before the commencement of treatment and at the end of four weeks of training. They include; Arabic version of Activities-Specific Balance Confidence Scale (A-ABC scale) to measure patient self-confidence for performing activities of daily living without losing balance. Permission has been granted from original author [name] by email to use the Arabic version of the ABC scale. It has proved its good reliability and validity and can be used with the Arab population's vestibular disorders (Alghwiri AA, Alghadir AH, Al-Momani MO and Whitney SL, 2015) (figure 2) (Appendix 3).

In addition, Berg Balance Scale (BBS) to evaluate static balance and fall risk in adult. It has shown good reliability and validity with vestibular patients too (Alghwiri AA, Alghadir AH, Al-Momani MO and Whitney SL, 2015) (figure 3) (Appendix 3).

Moreover, Katz Index of Independence in Activities of Daily Living (Katz ADL) to define problems in performing ADLs. It has demonstrated excellent validity and reliability to assess the ability to perform daily living activities independently in adult and older community-dwelling populations (Hopman-Rock M, van Hirtum, H, de Vreede P and Freiberger E, 2019) (figure 4) (Appendix 3).

## **2.6 Data analysis**

Data will be collected, tabulated, and analyzed using SPSS version 25. The descriptive data will be represented as mean (*M*) and standard deviation (*SD*). Paired *t*-test will be run to compare pre-intervention and post-intervention scores of A-ABC, BBS& Katz-ADL for each participant. Pearson’s r regression will be used to detect the linear association between variables. Results will be statistically significant at p <0.05.

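### No primary outcome is named and p <0.05 applies to every result, so the scale that decides the effectiveness claim can be chosen after the data are seen

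*Protocol*

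**What the plan says.** Protocol section 2.5 introduces the three scales under one sentence: "The following outcome measures for each participant will be evaluated before the commencement of treatment and at the end of four weeks of training". A-ABC comes first, for balance confidence; BBS second, for static balance and fall risk; Katz ADL third, for problems in daily activities. None is called primary or secondary. The Methods part of the abstract lists the same three, again without rank.

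Section 2.6 says that a paired t-test "will be run to compare pre-intervention and post-intervention scores of A-ABC, BBS& Katz-ADL for each participant". It adds that a Pearson "regression will be used to detect the linear association between variables", without naming the variables or the number of pairs. One threshold then covers everything: "Results will be statistically significant at p <0.05".

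The study aim in the abstract is to establish whether the combined exercise programme is effective. Section 1.4 (Objectives) puts balance and falls first and then adds activities of daily living. Section 2.1 describes the design: "This research is experimental with Pre-post cohort design, Pilot clinical trial, by using telerehabilitation". Section 2.3 justifies the 20 participants by precedent: "The sample size is the same as previous studies". The protocol states no testing order and no rule for how many scales must succeed.

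**The concern.** The aim asks one question, but three tests can answer it, and each is judged at 0.05 on its own. If one scale reaches p <0.05 and the other two do not, nothing written in advance prevents that scale from being presented as the effectiveness result. Two things are at stake. The deciding outcome can be chosen after the data are seen, and the 0.05 threshold then no longer describes the error risk of the overall conclusion.

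This matters more than usual here. With 20 volunteers, no control group and no power calculation, fixing the main question in advance is one of the few safeguards open to the study.

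A SAP that is not shown might hold adjustment details. However, the main outcome is normally fixed in the protocol, and this protocol is not silent on the threshold: section 2.6 sets 0.05 for all results. A later SAP would have to override that rule.

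**Working it through.** **Inputs from the protocol**
- Pre-post tests: k = 3 paired t-tests (section 2.6).
- Threshold: 0.05 for each result (section 2.6).
- Participants: n = 20 in a single group (sections 2.1 and 2.3), so 19 degrees of freedom per test.

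**Assumptions, because the protocol gives no figure**
- Tests are two-sided.
- There is no true change on any scale.
- The three change scores are normal with a common pairwise correlation ρ, varied from 0 to 1.
- All 20 participants complete.

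There is no figure in the plan to reproduce. The 0.05 is an input, and the protocol states no overall error rate.

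**Step 1. Independent tests.** The chance of at least one false positive is 1 − (1 − 0.05)^3 = 1 − 0.857375 = 0.1426, or 14.3%. Whatever the correlation, it cannot exceed 3 × 0.05 = 15%.

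**Step 2. Correlated tests.** This was simulated with 200,000 trials per setting and n = 20. A false positive is any |t| above the two-sided 5% critical value on 19 degrees of freedom. A false improvement is any t above the same value in the favourable direction, so the rate for a single test is 2.5%.

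| ρ | At least one false positive | At least one false improvement |
|---|---|---|
| 0 | 14.3% | 7.4% |
| 0.3 | 13.7% | 6.9% |
| 0.5 | 12.7% | 6.3% |
| 0.7 | 11.2% | 5.5% |
| 0.8 | 10.0% | 5.0% |
| 0.9 | 8.5% | 4.3% |
| 1.0 | 5.0% | 2.5% |

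**Step 3. If one scale hardly varies.** Participants who are already independent are eligible (section 2.2.1), so Katz might barely move; this is an assumption. The family is then in effect two tests: 1 − 0.95^2 = 0.0975, or 9.75% if they are independent.

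**Step 4. The Pearson tests.** They share the threshold but are not counted above. If, for illustration, there were three of them and all six tests were independent, the rate would be 1 − 0.95^6 = 0.265, or 26.5%. The protocol does not give the number, so this shows only the direction.

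**Step 5. What each remedy would cost.** With n = 20 and 80% power, the smallest detectable mean change, in SD units of the change score, is 0.66 for one primary test at 0.05. For a three-way Bonferroni split at 0.05/3 = 0.0167 it is 0.78, about 19% larger (0.784/0.660 = 1.19). The split holds the family rate at 1 − (1 − 0.0167)^3 = 4.9% for independent tests. Naming one primary holds the error on the primary question at 5% and keeps the 0.66.

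**The case against.** **Separate questions.** Section 1.4 sets daily living apart from balance and falls, and section 2.5 gives each scale its own construct. If each scale answered its own question, 0.05 per test would be defensible. That stands as far as it goes. However, the study aim still asks for one verdict on effectiveness, and no text says how three answers combine into it. A reader might infer that the plan declares success if any one scale is significant. It states no such rule; it only leaves that reading open.

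**No promise of 5% overall.** A reader might also infer that the protocol claims a 5% overall error rate and breaks it. It does not: the threshold in section 2.6 is set per result.

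**Pilot study.** Familywise control is not generally expected of a pilot, and this one has 20 convenience volunteers and no power calculation. That lowers the seriousness. It does not remove the point, because the protocol states effectiveness aims and a significance rule, states no feasibility objective, and nowhere calls its tests exploratory.

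**The size is conditional.** It is tempting to say flatly that the error rate is 11-14%. The documents do not support that: the range needs correlations from 0 to about 0.7, and none is given. It also counts false worsening, which would not support an effectiveness claim.

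**Not the main risk.** In a single-group pre-post design, the t-test asks whether scores changed, not whether treatment changed them. This stands in full. Change from other causes would make rejection more likely on every scale, including a named primary.

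**Conclusion.** The point holds in limited form. The protocol names no deciding outcome and applies 0.05 to every result, while seeking one conclusion on effectiveness. The size depends on assumptions that the protocol does not settle. With two-sided tests, no true change and three normally varying change scores, the excess over 5% is substantial at low to moderate correlation and shrinks to nothing as the correlation approaches 1. For false improvement, the rate is roughly two to three times the single-test 2.5% over correlations 0 to 0.7. The freedom to choose the outcome afterwards does not depend on these figures. Given the pilot label, this is a correction the sponsor should make before enrolment, not a flaw that invalidates the study.

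**What to change.** In section 2.5, name one primary outcome before the first patient is enrolled. BBS change at four weeks is the natural candidate, because the first objective in section 1.4 concerns balance and falls and section 2.5 assigns BBS to static balance and fall risk. In section 2.6:

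- Test the primary at 0.05.
- Test A-ABC at 0.05 only if the primary is significant.
- Report Katz ADL and all Pearson correlations descriptively.
- Give the mean change with a 95% confidence interval for every scale.

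If the sponsor intends a purely exploratory pilot, the alternative is to say so: call all tests exploratory and draw no effectiveness conclusion from any single p-value.

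The cost is a few sentences in the two sections. The primary loses no power, whereas a Bonferroni split would. The real price is that A-ABC cannot be claimed as significant if the primary fails, whatever its own p-value, and that Katz supports no significance claim.

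The change controls multiplicity and selective choice of outcome only. It does not enable a single-group study to separate the effect of treatment from other causes of change.
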